### **5.4 Subject Replacement**

In this study, subjects who are enrolled but not treated and subjects who discontinue treatment before completion of cycle 1 in Phase I for reasons other than the occurrence of a DLT may be replaced. Any replacement subject will be enrolled in the same dose group.

## **6 STUDY TREATMENT**

### **6.1 Allocation to Treatment**

Subjects in this study will be identified by a subject number. Each subject in this study will receive a unique subject number after signing the informed consent. Subject and treatment numbers will be assigned in chronological order starting with the lowest number in phase 1 study. Once a subject number and treatment number have been assigned to a subject, it cannot be reassigned to any other subject.

Dose level assignment will be performed centrally by the sponsor or its designated representatives. The study site will receive confirmation of enrollment along with the next available date for dosing and the assigned dose level from the sponsor or its designated representatives. Sponsor or its designated representatives will notify the other sites for the enrollment of a new subject and the next possible enrollment date.

### **6.2 Investigational Product D-1553**

#### **6.2.1 Formulation, Appearance, Packaging and Labeling**

The investigational product D-1553 will be supplied by InventisBio. The drug product is formulated as yellow, round tablets containing an equivalent of either 50 mg or 200 mg of D-1553 each [REDACTED]

The contents of the label will be in accordance with all applicable regulatory requirements.

#### **6.2.2 Handling and Storage**

The investigational product will be dispatched to a study center only after receipt of the required documents in accordance with applicable regulatory requirements and the sponsor's procedures.

Investigational product must be dispensed or administered according to procedures described herein. Only subjects enrolled in the study may receive investigational product, in accordance with all applicable regulatory requirements. Only authorized study center personnel may supply or administer investigational product. All investigational products must be stored in a secure area with access limited to the investigator and authorized study center personnel and under physical conditions that are consistent with investigational product-specific requirements. [REDACTED]

[REDACTED] Details of handling and storage information can be found in the label of the investigational product package.

### **6.2.3 Product Accountability**

The investigator or designee will manage investigational product inventory and accountability. Logs will be provided by the sponsor or its contractors, or site use same template from standard operating procedure (SOP) with sponsor approval. The drug product distribution and log will be managed centrally by a designated contractor/vendor.

The investigator or designee will maintain accurate records of receipt of all test articles, including dates and amounts of receipt. In addition, accurate records will be kept regarding when and how much investigational product is dispensed and used by each subject in the study. At the completion of the study, to satisfy regulatory requirements regarding investigational product accountability, all investigational product will be reconciled and retained or destroyed according to applicable local, provincial and federal regulations.

The investigator or designee agrees to dispense and administer investigational product only to subjects under his/her personal supervision. The investigator will not supply investigational product to any person not authorized to receive it and will not use product for any purpose other than that permitted in the protocol. All investigational product must be kept in a secure room with a temperature controlled and access restricted to only necessary study site personnel. Used and unused investigational product and corresponding containers will be stored securely in the study centers. All investigational products will be disposed of by the sponsor or its contractors after the completion of the study.

### **6.2.4 Administration**

In Phase 1a, each subject will receive daily oral doses of D-1553 (once -daily for Cohorts 1 to 4 and twice -daily for Cohorts 5 to 7) from Day 1 to Day 21 as one cycle on an empty stomach (no food and drink, except for water, for at least 0.5 hours before and after dosing) (Table 6-1). In Phase 1b, each subject will receive oral doses of D-1553 every day at recommended dose and schedule based on Phase 1a results in combination with other drugs. In Phase 2, each subject will receive oral doses of D-1553 every day at single agent RP2D or combination RP2D. All D-1553 doses should be taken on an empty stomach. On days when the subject is scheduled for a visit, D-1553 should be administered orally in the presence of the site personnel, especially when blood is collected for PK analysis. During the study, D-1553 should be taken at approximately the same time each day without treatment breaks until unacceptable toxicity, disease progression or withdrawal from the study. In the twice-daily schedule, D-1553 should be taken approximately 12 hours apart ( $\pm 3$  hours).

If a subject misses a dose, the dose will not be “made up” nor doubled at the next dose. If a subject vomits after taking a dose, the dose will not be “made up”, but the subject is to resume subsequent doses at the next day as prescribed.

Subjects will be instructed to swallow D-1553 tablets as a whole without chewing prior to swallowing. No tablet should be ingested if it is broken, cracked or otherwise not intact.

**Table 6-1 Phase 1a (Dose Escalation)**

| Dose Levels | Dose Levels        | Tablets Required       |
|-------------|--------------------|------------------------|
| Cohort 1    | 150 mg once-daily  | 3 × 50 mg              |
| Cohort 2    | 300 mg once-daily  | 1 × 200 mg + 2 × 50 mg |
| Cohort 3    | 600 mg once-daily  | 3 × 200 mg             |
| Cohort 4    | 1200 mg once-daily | 6 × 200 mg             |
| Cohort 5    | 400 mg twice-daily | (2 × 200 mg) × 2       |
| Cohort 6    | 600 mg twice-daily | (3 × 200 mg) × 2       |
| Cohort 7    | 800 mg twice-daily | (4 × 200 mg) × 2       |

### 6.2.5 Discontinuation of Study Treatment

All study subjects may continue to receive daily D-1553 until unacceptable toxicity, disease progression or withdrawal from the study whichever occurs first. Subject may withdraw from the study at any time with or without reason. The investigator may withdraw any subjects from the study in the subject's best interest where continuation would place the subject in danger. If the investigator judges the subject is benefiting from study treatment after equivocal disease progression, study treatment may continue after discussion with the sponsor medical monitor. The decision to continue treatment beyond initial investigator-assessed progression and the subject's agreement should be documented in the study records.

### 6.2.6 Dose Modification

Every effort should be made to administer D-1553 at the planned dose and schedule (Table 6-2). In the event of significant toxicity, dosing may be delayed and/or reduced as described below. In the event of multiple toxicities, the dose modification should be based on the worst toxicity observed (according to the NCI CTCAE v5.0). Whenever possible, dose and scheduling modifications should be discussed between the investigator and the sponsor prior to implementation. Subjects are to be instructed to notify investigators at the first occurrence of any adverse symptom. After dose reduction for toxicity, the D-1553 dose for that subject will not be re-escalated.

Up to two dose reductions of D-1553 due to toxicity will be allowed before the subject must be permanently discontinued from the study. Any further dose reduction, if the investigator judges to be beneficial to the subject, must be discussed with the sponsor's medical director.

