18. These procedures can be done on Day -1 or Day 1 but have to be completed prior to first dose of study intervention. They are intended for checking the subject status before the first dose, not for eligibility. A subject's eligibility should be determined during the screening period. Laboratory tests performed in the screening period within 7 days of Day 1 do not need to be repeated on Day -1 or Day 1 unless clinically indicated.
19. These visits need to be completed within 7 days of the last dose of study intervention:
  - a. Subjects who stop treatment due to disease progression at the visit time do not need to repeat the imaging examination;
  - b. The radiologic imaging examination needs to be repeated if more than 4 weeks have passed from the last examination to the end of treatment visit;
  - c. Other examinations are required to be repeated if more than 1 week from last examinations.
20. A follow-up phone call is allowed to perform the check on AE status and concomitant medications.
21. Subjects who do not have disease progression on study will be followed for tumor assessment, approximately every 12 weeks ( $\pm 2$  weeks), until disease progression, death, lost to follow-up, start of another anticancer therapy, or other reasons that a follow-up is not possible.
22. Subjects will be followed for survival status monthly ( $\pm 2$  weeks), until death, lost to follow-up or other reasons that a follow-up is not possible. The follow-up can be done via telephone call.
23. [REDACTED]
24. Plasma ctDNA is to be collected pre-dose as indicated in the Schedule of Assessments (Screening, Day 1 of Cycle  $\geq 2$  and EOT). [REDACTED]

25. Subjects will provide archived FFPE samples (collected within 5 years) for KRASG12C mutation confirmation that enables KRASG12C testing prior to starting all other screening procedures.
26. Testing for HIV, Hep B and Hep C should be conducted during Screening for eligibility determination. A positive HBsAg will be considered positive for Hep B. A positive anti-HCV antibody and anti-HIV antibody will be considered positive for Hep C and HIV, respectively. [REDACTED]  
[REDACTED]

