### 5.3 Subject Completion and Withdrawal

#### 5.3.1 Subject Completion

In the dose escalation part of this study, a subject will be considered complete if he/she has a valid PK profile and has not withdrawn from the study prior to completing DLT observation period (at least one cycle). A subject will also be considered complete if he/she discontinued study treatment due to a DLT with or without a valid PK profile.

In other parts of the study, a subject is considered to have completed the study if he/she has completed study treatment as defined in the protocol, experienced disease progression, started another anticancer treatment, or been withdrawn by the investigator or sponsor for administrative reasons.

The end of the study for each subject is defined as the last visit of each subject. The end of the study is defined as the date of the last visit of the last subject in the study or last scheduled

procedure shown in the Schedule of Activities (SoA, Table 1-1 and Table 1-2 for Phase 1, Table 1-3 and Table 1-4 for Phase 2) for the last subject in the trial globally.

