### **5.3.2 Subject Withdrawal**

A subject may withdraw from the study at any time at his/her own request or may be withdrawn at any time at the discretion of the investigator for safety, behavioral or administrative reasons. The subject will be definitively discontinued from both the study intervention and from the study at that time. If the subject withdraws from the study intervention, survival follow up may still be conducted until death, lost to follow-up or other reasons that a follow-up is not possible.

If the subject withdraws consent for disclosure of future information, the sponsor may retain and continue to use any data collected before such a withdrawal of consent.

If a subject withdraws from the study, he/she may request destruction of any samples taken and not tested, and the investigator must document this in the site study records.

At the time of discontinuing from the study, if possible, an early discontinuation visit should be conducted, as shown in the SoA (Table 1-1 and Table 1-2 for Phase 1, Table 1-3 and Table 1-4 for Phase 2).

Refer to the SoA (Table 1-1 and Table 1-2 for Phase 1, Table 1-3 and Table 1-4 for Phase 2) for data to be collected at the time of study discontinuation and follow-up and for any further evaluations that need to be completed.

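### Sections 6.2.6 and 5.3.2 take some subjects off the study where the Phase 2 schedule requires continued tumor and survival follow-up; Section 5.3.1 adds ambiguity for OS

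*Protocol*

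**What the plan says.** **Exit wording.** Section 6.2.6 states: "Up to two dose reductions of D-1553 due to toxicity will be allowed before the subject must be permanently discontinued from the study". The next sentence softens this: "Any further dose reduction, if the investigator judges to be beneficial to the subject, must be discussed with the sponsor's medical director".

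Section 5.3.2 covers two groups in one paragraph: subjects who leave at their own request, and subjects withdrawn by the investigator for safety, behavioral or administrative reasons. For both it says: "The subject will be definitively discontinued from both the study intervention and from the study at that time". It then adds: "If the subject withdraws from the study intervention, survival follow up may still be conducted until death, lost to follow-up". It says nothing on tumor assessment after either kind of exit, beyond a general reference to the schedules.

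Section 5.3.1, for all parts other than dose escalation, says that "a subject is considered to have completed the study if he/she has completed study treatment as defined in the protocol, experienced disease progression". The list goes on to "started another anticancer treatment, or been withdrawn by the investigator or sponsor for administrative reasons". The same section also says: "The end of the study for each subject is defined as the last visit of each subject".

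**Follow-up wording.** For Phase 2, Section 4.1.3, Table 1-3 (footnotes 21 and 22), Table 1-4 (footnotes 26 and 27) and Section 7.2.9 require two things:

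- Tumor assessment about every 12 weeks in subjects without progression, until progression, death, loss to follow-up, new anticancer therapy or follow-up not being possible.
- Survival follow-up: "Subjects will be followed for survival status monthly", until death, loss to follow-up or follow-up not being possible.

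PFS, DOR and OS are secondary endpoints of Phase 2 (Section 3.4.2), analysed by Kaplan-Meier (Section 9.4.5). The primary endpoint is ORR.

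**The concern.** A subject whose allowed reductions are used up, or whom the investigator withdraws for safety, may well be free of progression and alive. The schedule says that such a subject is still scanned and called. The exit wording says that the subject has left the study. A site cannot do both, and the catch-all in the follow-up text (follow-up not possible) lets it treat the exit as a valid reason to stop.

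These exits are plausibly related to prognosis, because they follow toxicity or a safety judgement. Kaplan-Meier estimates assume that censoring is unrelated to prognosis, so PFS, DOR and OS would be at risk of informative censoring if sites followed the exit wording. An analysis plan can choose censoring rules, but it cannot recover scans and calls that were never made. The protocol is therefore the right place to settle the point.

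**Working it through.** The protocol states no dropout, censoring or event figure for PFS or OS, so there is nothing to reproduce. The check is a comparison of passages, followed by an illustration of size.

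**Step 1: the passages side by side**

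| Situation | Exit text | Phase 2 schedule | Endpoint touched |
|---|---|---|---|
| Reductions used up, no further one agreed | 6.2.6: off the study | Scans and monthly survival continue | PFS, DOR, OS |
| Investigator withdraws the subject, for example for safety | 5.3.2: off treatment and study | Scans and monthly survival continue | PFS, DOR, OS |
| Subject stops only the intervention | 5.3.2: survival optional (*may*), scans not mentioned | Both required (*will*) | PFS, DOR, OS |
| Progression | 5.3.1: completed | PFS event has occurred; survival continues | OS only |
| New anticancer therapy | 5.3.1: completed | Already a listed stop for scans; survival continues | OS only |

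The first two rows are direct conflicts. The third is optional against required for OS, and silence against required for scans. The last two are ambiguities, because Section 5.3.1 defines completion and does not instruct anyone to stop follow-up.

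**Step 2: how large the effect could be (illustration only)**

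Inputs: a median PFS of 4.0 months and a median OS of 10.7 months, from the cited second-line cetuximab plus irinotecan study in Section 2.3. They serve as a scale and are not this trial's assumptions. Times are taken as exponential, with PFS hazard λ = ln 2 / 4.0 = 0.173 per month. All other inputs below are assumed.

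*PFS censored at a toxicity exit.* Let s be the share of subjects whose first event is the exit, so the exit hazard is g = sλ/(1 − s). Let k be the ratio of the PFS hazard after exit to that before. The Kaplan-Meier estimate that censors at exit has a median of 4.00 months. The true curve is S(t) = e^(−(λ+g)t) + g[e^(−kλt) − e^(−(λ+g)t)]/(λ + g − kλ). Its medians in months are:

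| s | k = 1.5 | k = 2 | k = 3 |
|---|---|---|---|
| 5% | 3.97 | 3.94 | 3.91 |
| 10% | 3.93 | 3.88 | 3.81 |
| 20% | 3.86 | 3.76 | 3.62 |

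The overstatement runs from 4.00 − 3.97 = 0.03 to 4.00 − 3.62 = 0.38 months.

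*OS if survival follow-up stopped at progression.* Let f be the share of PFS events that are deaths. Kaplan-Meier then sees only deaths without prior progression, with hazard fλ, so the apparent median is ln 2/(fλ) = 4.0/f. Against a true median of 10.7 months:

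| f | Apparent OS median (months) | Apparent survival at 10.7 months (true 0.50) |
|---|---|---|
| 5% | 80 | 0.91 |
| 10% | 40 | 0.83 |
| 20% | 20 | 0.69 |
| 30% | 13.3 | 0.57 |

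This second case needs sites to let the completion wording of Section 5.3.1 override the survival schedule.

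**The case against.** The best defence is that the schedule already governs. Section 7.2.8 covers subjects who stop for an unacceptable adverse event, and Section 7.2.9 then provides for scans and monthly calls. Section 5.3.2 refers the reader to the schedules and partly separates withdrawal from the intervention from withdrawal from the study. Section 5.3.1 ends each subject's study at the last visit, and the trial at the last visit or last scheduled procedure; the Phase 2 schedules include an OS column. The affected endpoints are secondary, with no stated power. Detailed methods are left to an analysis plan that is not at hand.

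Much of this stands, and it rules out four stronger readings that a reader might infer:

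- *That Section 5.3.1 contradicts PFS follow-up.* It does not. Progression is the PFS event, and new therapy is already a listed stop for scans.
- *That OS information is lost for nearly all subjects who progress.* This treats a completion definition as overriding four explicit follow-up passages. Even on that reading, subjects who progress would still contribute OS time up to progression.
- *That leaving after two reductions is automatic.* The next sentence of Section 6.2.6 allows further reductions after discussion.
- *That the exit rules cause informative censoring.* None of the three sections says that PFS or OS is censored at these exits. It is a risk that depends on what sites do.

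What the defence does not remove is the wording itself. Section 6.2.6 says study where the schedule needs treatment. Section 5.3.2 takes subjects withdrawn by the investigator off the study, and Section 6.2.5 likewise lets the investigator withdraw subjects from the study for their safety. The optional survival sentence in Section 5.3.2 does not preserve scans.

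**Conclusion.** The conflict is real for Sections 6.2.6 and 5.3.2 against the Phase 2 follow-up text, and it touches PFS, DOR and OS. Section 5.3.1 is ambiguous for OS only. The consequence is a risk of informative censoring if sites follow the exit wording.

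Its size cannot be derived from the protocol. On the assumed inputs, the effect of toxicity exits on PFS is small (0.03 to 0.38 months on 4.0). The effect on OS could be large (an apparent median of 13.3 to 80 months against 10.7), but only if survival follow-up stopped at progression, which the schedule does not provide for. Primary ORR is little affected. The point is worth correcting because lost follow-up cannot be repaired at analysis, but it does not threaten the main conclusion of Phase 2.

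**What to change.** Reconcile the passages by defining stopping treatment separately from leaving the study.

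- **Section 6.2.6:** write *discontinued from study treatment* in place of the reference to the study.
- **Section 5.3.2:** split the two groups. For subjects withdrawn by the investigator, or who stop only the intervention, state that scheduled tumor assessments (until progression or the other stops already listed) and survival follow-up *will* continue. State that subjects who withdraw from the study at their own request keep the right to end all follow-up, so that follow-up is not extended to them by default.
- **Section 5.3.1:** state that completion at progression or new therapy does not end Phase 2 survival follow-up. Do not tie the end of treatment to progression here, because Section 6.2.5 allows treatment to continue after equivocal progression.

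No dose rule, treatment-stopping rule or provision for treatment beyond progression is changed. The cost is wording in three paragraphs of an amendment; the scans and calls are already in the schedule.

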**Table 6-2 Dose Modification Table**

| Starting Dose Level                   | Dose      |            |            |            |
|---------------------------------------|-----------|------------|------------|------------|
|                                       | 600 mg QD | 1200 mg QD | 400 mg BID | 600 mg BID |
| Dose Reduction Level 1         | 400 mg QD | 400mg BID  | 600mg QD   | 400 mg BID |
| Dose Reduction Level 2 (Daily) |           | 600 mg QD  | 400mg QD   | 600 mg QD  |

\*This table is just for reference. The actual dose modification plan of each individual case should be discussed with

sponsor's medical monitor.

Dose modifications may occur:

- Within a cycle: dose interruption until adequate recovery during a given treatment cycle;
- Between cycles: next cycle administration may be postponed due to toxicity in the previous cycle.

### 6.2.7 Dose Interruptions/Delay/Reductions

Dose reductions of D-1553 may be required based on the worst toxicity experienced. In the event that a study drug related Grade 3 or higher toxicity occurs, defined in the NCI CTCAE v5.0, administration of D-1553 should be held until the drug related toxicity has resolved to grade 1 or baseline. Upon resolution of the toxicity or return to baseline, the subject should resume their current assigned dose of D-1553 or at the next lower dose level after discussion with sponsor. The following guidance can be used:

- After Cycle 1 Day 1, a treatment delay or dose interruption of more than one treatment cycle (21 or 28 days after the current cycle) will result in treatment discontinuation unless the subject is receiving clinical benefit as judged by the investigator and after discussion with the sponsor.
- Doses delayed or missed will not be made up (i.e., cycles will not be prolonged beyond the 21st or 28th calendar day in order to make up any missed doses).
- If a treatment interruption continues beyond Day 21 or Day 28 of the current cycle, then the day when treatment is resumed will be counted as Day 1 of the next cycle.

For subjects who experience a recurrent study drug related Grade 3 or higher toxicity, a discussion between the sponsor and investigator will occur to determine whether the subject should continue in the study. For any subject experiencing a Grade 3-4 toxicity, treatment should be resumed at next lower dose level after toxicity resolves to Grade 1 or baseline. A subject who experiences the same serious adverse event (SAE) of the same NCI CTCAE toxicity grade or higher related to D-1553 must discontinue the treatment immediately. Any subject with liver function test abnormalities meeting Hy's Law\* criteria [REDACTED]

[REDACTED] must be permanently discontinued,  
[REDACTED]  
[REDACTED]  
[REDACTED]

\* Hy's Law: ALT or AST  $\geq 3 \times$  ULN, TBIL  $\geq 2 \times$  ULN in the absence of cholestasis (serum alkaline phosphatase [ALP]  $> 2 \times$  ULN), and there are no other reasons to explain the combined elevation of aminotransferase and TBIL.

[REDACTED]

In combination cohorts, the combination drugs (other than D-1553) may have dose interruption, delay, reduction or other modifications according to their prescribing information.

[REDACTED]

[REDACTED]

\_\_\_\_\_

\_\_\_\_\_

[REDACTED]

\_\_\_\_\_

\_\_\_\_\_

[illegible]

[illegible]

